#### Measurement of resource use

For the intervention costs, an ingredients approach will be used to estimate resources. Routine data linked to intervention protocols will be collected and used to assess resources directly consumed in the provision of the intervention, including supplies, manuals and patient education materials. Facility observations of intervention delivery will be conducted for the economist to understand the intervention and the facility context; these observations will complement intervention cost data collection. The costs of intervention focused counsellor training and facility-level institutional strengthening and capacity development through organisational readiness workshops^41^ will be included in the cost analysis as start-up costs^42^ in order to capture the full economic costs of integrating the intervention into the primary care service for patients with chronic disease.^42^

A time and motion tool (TMT) developed for this evaluation will measure counsellor time usage in delivering the intervention for both active arms in the study. Time tools have been used in analysis of human resource requirements for expanding access to HIV^43^ and TB care^44^ using lay health workers and have proved useful in highlighting the scope of duties of this cadre. To our knowledge, there is limited evidence in the South African context on time costs of CHW-delivered mental health counselling. The TMT will enable an analysis of differences in counsellor time usage in the different intervention modalities, indicating opportunities for scale and scope efficiencies. It is anticipated that the costs associated with the TAU option will be minimal and any referral costs will be captured through patient self-report of services they have used.

For the HIV and diabetes services, a step-down methodology will be used to establish resource use. Staff time will be determined through review of facility organograms and interviews with senior managers. In addition, utilisation of HIV and diabetes medicine and diagnostics will be estimated by applying standard treatment guidelines/protocols for HIV and diabetes treatment in primary care services to utilisation statistics obtained from facility records (ie, protocol-based facility utilisation statistics)

Establishing the use of referral services is challenging given that there is no health information system that enables patient pathways through care to be established. Therefore, to establish patient utilisation of health services beyond their HIV and diabetes care at the primary level, we will administer a patient questionnaire developed for the study at baseline, and at the 6-month and 12-month assessments. Using this questionnaire, we will capture health service utilisation for other primary care services (eg, TB treatment), hospital services, emergency department care, paramedic care and referrals to mental health providers. Patients will be asked to quantify the number of these additional visits, and lengths of stay in hospital. Given concerns with patient recall, we have asked patients to estimate their usage of ambulatory services over the previous month and have used a recall period of 6 months for inpatient services. These data will then be extrapolated to estimate costs over the time horizon.

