### MIND economic evaluation

#### Objective

The study will be a prospective economic evaluation. The objectives include estimating:Full economic provider costs of the mental health intervention; any cost offsets attributable to the intervention related to changes to the costs of HIV or diabetes care at the primary care level and changes to the costs of referral care (including tuberculosis (TB), emergency department and inpatient care).Patient costs: associated with the intervention which will include direct out-of-pocket payments to private health providers (consultations and medications, etc), travel and subsistence costs and productivity losses.Cost-effectiveness in terms of the incremental cost per unit of improvement in disease-specific outcome (CES-D, AUDIT, HIV-1 RNA, HbA1c).Cost-utility in terms of the incremental cost per quality-adjusted life year (QALY) gained.Budget impact of scaling up the intervention.

To achieve these objectives, the incremental cost-effectiveness ratio (ICER) will be calculated by ordering the MIND_DED, the MIND_DES and MIND_TAU alternatives from least cost to highest cost and calculating the difference in costs and outcomes against the next less costly, non-dominated alternative or against the common baseline of MIND_TAU.

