### Estimating costs for the provider’s perspective

Within economic evaluation, the appropriate scope of provider costs includes all costs incurred within the intervention and any changes in broader health system costs that can be attributable to the intervention. We have categorised these costs as intervention costs, HIV and diabetes service costs and other related provider costs. As shown in table 1, our approach to estimating these costs entails the measurement of quantities of resources that are used, and multiplying these quantities by the value (or unit cost) of each resource. These separate steps of measurement and valuation are described below.

**Table 1 T1:** Measuring and valuing provider costs

Cost component	Measurement		Valuation	
	Resources used	Quantities or utilisation	Valuation data	Allocation factor
Intervention				
Capital costs				
Facility readiness workshops	Number of staff	Time from trial data	Cost of employment converted to annual equivalent cost	DED/DES/TAU headcount
Intervention training for counsellors	Number of counsellors	Time from trial data	Cost of employment converted to annual equivalent cost	DED/DES/TAU headcount
Counselling room	Space	Square metres	Replacement value converted to annual equivalent cost	DED/DES/TAU headcount
Furniture and equipment	Tape recorders	Inventory	Replacement value converted to annual equivalent cost	DED/DES/TAU headcount
Vehicles	Vehicles	Inventory	Replacement value converted to annual equivalent cost	DED/DES/TAU headcount
Recurrent costs				
Counselling personnel	Number of staff (lay counsellors; registered counsellors; clinical psychologist)	Time from time and motion tool	Cost of employment×proportion of time	DED/DES/TAU headcount
Counselling supplies	Manuals, notebooks, pens	Number used—from trial data	Market value	DED/DES/TAU headcount
Non-intervention personnel	Number of staff	Time from facility data	Cost of employment×proportion of time	Facility headcount
Utilities	Electricity, water, other utilities, phone, cleaning, transport and stationery	Facility utilisation	Annual facility expenditure	Facility headcount
HIV/Diabetes service				
Capital costs				
Buildings	Space used for HIV/diabetes service	Square meters	Replacement value converted to annual equivalent cost	HIV/Diabetes headcount
Equipment and furniture	Equipment and furniture used for HIV/diabetes service	Inventory	Replacement value converted to annual equivalent cost	HIV/Diabetes headcount

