Vehicles	Vehicles used for HIV/diabetes service	Inventory	Replacement value converted to annual equivalent cost	HIV/Diabetes headcount
Recurrent costs				
HIV/Diabetes personnel	Number of staff and staff time spent on HIV/diabetes service	Time from facility data	Cost of employment ×proportion of time	HIV/Diabetes headcount
Drugs	ARV/Diabetes medication	Treatment protocol	National tender prices	Direct allocation
Diagnostic tests	CD4 test, diabetes monitoring tests, etc	Treatment protocol	National Health Laboratory Service prices	Direct allocation
Non-HIV/diabetes personnel	Managerial, cleaning and security staff	Facility utilisation	Facility expenditure	Facility headcount
Building operating and maintenance	Electricity, water, other utilities, phone, cleaning, transport and stationery	Facility utilisation	Facility expenditure	Facility headcount
Other related healthcare providers				
Public clinic visit	Average cost per visit	Patient interviews	Facility expenditure	Facility headcount
Public hospital ER/OPD visit	Average cost per OPD visit	Patient interviews	Facility expenditure	Facility Inpatient days and Outpatient headcount
Public hospital inpatient day	Average cost per inpatient day	Patient interviews	Facility expenditure	Facility Inpatient days and Outpatient headcount

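### The HIV/diabetes primary-care cost offset promised in the objectives cannot be identified from the resource-use data that the article describes

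*Protocol article*

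**What the plan says.** **The aim.** The Objective section lists, within provider costs, "any cost offsets attributable to the intervention related to changes to the costs of HIV or diabetes care at the primary care level", alongside changes in referral care. The section on costs from the provider's perspective repeats the scope: intervention costs plus "any changes in broader health system costs that can be attributable to the intervention".

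**The method for HIV and diabetes services** (Measurement of resource use, and Table 1):
- In general, "a step-down methodology will be used to establish resource use".
- For personnel, "Staff time will be determined through review of facility organograms and interviews with senior managers".
- For drugs and diagnostics, "utilisation of HIV and diabetes medicine and diagnostics will be estimated by applying standard treatment guidelines/protocols for HIV and diabetes treatment", and these guidelines are applied "to utilisation statistics obtained from facility records (ie, protocol-based facility utilisation statistics". Table 1 gives the treatment protocol as the quantity source, with national tender or laboratory prices.
- Buildings, equipment, vehicles and service personnel are allocated by "HIV/Diabetes headcount".

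**The participant data.** A questionnaire at baseline, 6 and 12 months is administered "to establish patient utilisation of health services beyond their HIV and diabetes care at the primary level". It covers other primary care such as TB treatment, hospital and emergency care, paramedics and mental health referrals.

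**The concern.** An offset attributable to the intervention is a difference between arms in what participants consume. To estimate it, at least one quantity in the costing must be able to differ because a participant received counselling. Every quantity described for primary-level HIV/diabetes care is instead a facility figure or a guideline figure, and the instrument that does observe participants is directed at other services.

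The offset is a central part of the argument. The Introduction justifies investment partly by lower chronic disease treatment costs, and the abstract promises cost per patient-year by arm and chronic disease to support a business case. A null offset produced by the costing method could be read there as evidence that no saving exists. The opposite error is equally possible. Adherence is a secondary outcome, and if better adherence led to more visits or dispensing, that added cost would be missed too.

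**Working it through.** The article gives no figure for the offset, so there is none to reproduce. The check follows what the stated method can return.

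**1. Algebra of the stated method.** Write the HIV/diabetes provider cost of participant *i* in facility *f* as the sum over services *k* of q(i,k) × p(f,k), where q is quantity and p is unit cost. The intervention can act on q. As described, q(i,k) is replaced by g(k), a guideline or facility-level quantity that does not depend on the participant's own use.

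- *Unit costs pooled over facilities:* arm difference = Σ g(k)p(k) − Σ g(k)p(k) = 0, whatever the true effect on q.
- *Unit costs facility-specific:* arm difference = Σ g(k) × [mean p(k) in one arm − mean p(k) in the other]. This is facility cost per head and contains no effect on q.

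The article does not say which applies. Neither identifies the offset.

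**2. Could participant use enter elsewhere?**

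| Place | What it offers | Does it supply q(i,k)? |
|---|---|---|
| Table 1, public clinic visit | Patient interviews | No: listed under other related providers |
| Table 1, direct allocation of drugs and tests | An allocation factor | No: the quantity is still the treatment protocol |
| Patient-perspective questionnaire | Time and out-of-pocket payments | Not linked to provider cost |
| Table 2, probabilistic rows | Intervention and referral utilisation | No HIV/diabetes service row |

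**3. Leakage through facility statistics.** Trial participants are also part of their facility's statistics, so a trace of the effect could enter. With even recruitment, 600/24 = 25 participants per disease per facility. If the facility average were used as the outcome, a true 20% fall in their use would move it by 0.20 × 25/H, where H is the service headcount. H is not given. Over an assumed range:

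- H = 250: 2.0%
- H = 500: 1.0%
- H = 1000: 0.5%
- H = 5000: 0.1%

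This only illustrates that the trace is small. A step-down unit cost acts as a price and is not meant to respond to 25 people.

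**4. What participant-level quantities would give (illustrative).** Assumptions: two arms of 8 facilities (24/3, equal allocation), 25 participants each, Poisson visits with mean 6 a year, a true 20% reduction, H = 1000, and between-facility unit-cost CV of 10%, 20% or 30%. Differences are in percent of the control mean.

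- *Facility averages, facility-specific unit costs:* expected difference 0.20 × 25/1000 = 0.5%. The SD is about CV × √(2/8), which is 5, 10 or 15 points. Simulation gave the same SDs.
- *Participant visits × common unit cost:* simulated mean about 20%. SD = √[(4.8 + 6)/200]/6 = 3.9 points; simulation gave about 4.
- *Participant visits × facility-specific unit cost:* simulated mean about 20%, SD about 6, 10 and 14 points.

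The SDs for participant data ignore facility differences in visit rates, so they are optimistic. The contrast in means, 20% against 0.5%, does not depend on that.

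**The case against.** The strongest reply is that participant data may exist. The patient-perspective questionnaire asks about time spent accessing care and is not expressly limited to services beyond HIV and diabetes. Costing travel and time for free primary care plausibly needs visit counts. The questionnaire is not shown, and the article condenses fuller trial documents. This stands to the extent that one cannot say such data are absent. But Table 1 gives source, valuation and allocation line by line, and no line brings such data into provider cost. The stated method conflicts with the stated objective; this is more than an omitted detail.

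A reader might go further and infer that arm differences would reflect clinic size and that every ICER would carry this noise. The documents do not support that. Drugs and tests use protocol quantities at national prices, so clinic size does not enter their price. Headcount-allocated lines differ by arm only if unit costs are facility-specific, which the article leaves open. Under pooling there is no noise, only a zero. Nor should the dilution percentages be read as the size of a bias, since the headcounts are assumed.

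The planned sensitivity analyses mention varying utilisation rates. Varying an assumed rate tests robustness but does not supply the missing observation of an effect.

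**Conclusion.** The concern holds for one component: the HIV/diabetes primary-care offset is not identifiable as described. Under pooled unit costs its estimate is exactly zero by construction. Under facility-specific unit costs it measures facility cost per head. In either case, no conclusion about an offset, positive, negative or null, would be warranted.

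This rests on reading Table 1 and the questionnaire's stated scope as the operative method. It does not depend on the assumed headcounts, visit rates or unit-cost variation. Intervention costs are unaffected, as are offsets in referral, TB, emergency and inpatient care, which come from participants' own reports. The listed limitations (recall, few referrals under usual care, short follow-up) do not cover this point.

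**What to change.** Obtain each participant's HIV/diabetes visits, current regimen and tests, either from items added to the 6- and 12-month questionnaire or from facility, pharmacy or laboratory records. If the patient-cost questionnaire already records such visits, link them to provider cost. Multiply the quantities by one unit cost per service applied equally in all arms, with facility-specific unit costs as a sensitivity analysis, and allow for clustering when comparing arms. Add HIV/diabetes service utilisation to the probabilistic rows of Table 2.

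The cost is a small respondent or extraction burden. The article writes of the utilisation recall questions partly in the past tense, so data collection may be under way. Items added now would cover only some participants and would share the self-report recall problem already acknowledged. Record extraction could also reach those already followed up, where records allow.

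If neither route is feasible, remove the HIV/diabetes primary-care offset from the objective, limit the offset claim to referral care, and state in the limitations that no conclusion about a primary-care offset can be drawn. That costs only wording.

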#### Intervention and comparator

The counselling programme delivered in MIND-DED and MIND-DES is based on motivational interviewing (MI) and problem solving therapy (PST).^28^ It is delivered in three sessions over 6 weeks with one optional booster session. The MI component provides psychoeducation about depression and hazardous alcohol use in relation to chronic disease, builds readiness for counselling and helps participants develop goals for counselling. The PST component targets maladaptive coping strategies and builds skills and strategies for dealing with life problems. Patients will receive individual face-to-face counselling from CHWs and take-home booklets to support self-learning between sessions. Registered psychological counsellors, supervised by psychologists, will train the counsellors.^24^ The underlying theory, content and evidence for the efficacy of the counselling approach for reducing symptoms of depression and hazardous/harmful alcohol use over the 1-year time frame have been described previously.^29–31^ In the TAU arm, the standard package of care will be provided to patients who are suspected of having mental health problems. In general, patients using the HIV or diabetes service are asked by a nurse or doctor attending to their care about their mental well-being, life stressors and use of alcohol or other substances. Patients are provided with advice to change their lifestyles. Where the healthcare provider deems it necessary, patients are referred to a mental health nurse for further assessment or screening. The patient may also be referred to a social worker who may refer them to non-governmental organisations (NGOs) who provide counselling and support services.^24^

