### Estimating costs for the patient perspective

#### Measurement of resource use

For the patient perspective, we will use a questionnaire at baseline, 6 and 12 months to estimate resource use. This will capture any user fees associated with public, private or NGO-provided health services as well as traditional and faith-based therapies. In addition, we will ask patients to estimate their time spent accessing healthcare services, as well as out-of-pocket payments for transport, subsistence and accommodation. Travel, subsistence and accommodation costs will relate to both the patient and their caregiver, if the patient is accompanied by a caregiver to any of these services.

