Potential challenges to this study include recall bias due to the reliance on patient-reported health service use for our estimations of service utilisation. To limit recall bias, a 1-month recall period will be used for ambulatory services and 6-month recall for hospitalisations.^52^ Another possible limitation is that only a few patients may be referred for mental healthcare for CMD in the TAU option so we may not fully capture referral costs thus potentially underestimating cost-effectiveness. Another potential limitation is that the short follow-up period of 12 months may not capture the extent of the benefit that patients and the health system could gain through the availability of this service. For example, the degree to which the socioeconomic benefits and the returns to mental health associated with such interventions^76^ may not be fully evident by the 12-month end point. This is a common problem associated with trial-based economic evaluations.^77^

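### The one-month ambulatory recall windows are unlikely to observe the counselling phase, so patient attendance costs in the two active arms may be omitted or distorted

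*Protocol article*

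**What the plan says.** All references are to the protocol article.

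- **Timing of measurement.** For care beyond primary-level HIV and diabetes services, Measurement of resource use (provider's perspective) says "we will administer a patient questionnaire developed for the study at baseline, and at the 6-month and 12-month assessments".
- **Recall.** The same section says "we have asked patients to estimate their usage of ambulatory services over the previous month", and that the authors "have used a recall period of 6 months for inpatient services". The Discussion repeats both periods: "a 1-month recall period will be used for ambulatory services and 6-month recall for hospitalisations".
- **Unobserved months.** "These data will then be extrapolated to estimate costs over the time horizon". The method is not given.
- **Patient costs.** Measurement of resource use (patient perspective) says "we will use a questionnaire at baseline, 6 and 12 months to estimate resource use". It covers time, transport, subsistence and accommodation, and gives no recall period of its own.
- **Counselling.** Intervention and comparator says "It is delivered in three sessions over 6 weeks with one optional booster session". It does not say when the first session falls relative to baseline, or when the booster is given.
- **Objective.** The second listed objective is "Patient costs: associated with the intervention which will include direct out-of-pocket payments to private health providers", with travel, subsistence and lost productivity also named.
- **Costing period.** Statistical analysis of costs and effects starts the accumulation of mean patient costs at baseline.

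**The concern.** The counselling visits are concentrated early, while the ambulatory windows sit just before enrolment, just before month 6 and just before month 12. A patient who attends every core session soon after enrolment would report none of them in any window. Scaling up months 5 to 6 and 11 to 12 cannot restore visits that took place only in the first weeks.

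The gap is one-sided. Counselling visits occur in the dedicated and designated arms and not under treatment as usual, so leaving out their time and travel cost lowers incremental patient cost for both active arms. The societal ratio, which the Perspective and Determining cost-effectiveness sections commit to present, would then look better than it should. If attendance is similar in the two active arms, the comparison between them is much less affected.

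A second, weaker effect concerns ambulatory referrals in the early months, which can arise in all three arms. Under treatment as usual, referral costs rest on patient self-report. Any early peak in referrals would fall between windows.

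**Working it through.** **Inputs from the article:** ambulatory recall 1 month; inpatient recall 6 months; questionnaires at 0, 6 and 12 months; three core sessions within 6 weeks; one optional booster. **Conversion:** 365.25 / 12 / 7 = 4.35 weeks per month. The article gives no figure of its own to reproduce on this point.

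**1. Ambulatory windows, in weeks from baseline**
- Baseline: −4.3 to 0 (wholly before enrolment)
- Month 6: 5 × 4.35 = 21.7 to 6 × 4.35 = 26.1
- Month 12: 11 × 4.35 = 47.8 to 12 × 4.35 = 52.2

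Follow-up coverage is 2 of 12 months, or 16.7%.

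**2. Overlap with the six-week core phase, by its start week s**

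The phase runs from s to s + 6. It misses the month-6 window if s + 6 ≤ 21.7, that is, s ≤ 15.7.

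| Start (weeks after baseline) | Overlap with ambulatory windows (weeks) |
|---|---|
| 0, 4, 8, 12, 15 | 0 |
| 16 | 0.3 |
| 18 | 2.3 |
| 20 | 4.3 |

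**3. What extrapolation does to counselling visits**

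If each follow-up month stands for six months, the multiplier is 6.
- Three core sessions, none in a window: 6 × 0 = 0 visits, against 3 attended.
- One booster in the month-6 window: 6 × 1 = 6 visits. With the core sessions the patient attended 3 + 1 = 4.

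So the error can run either way for one patient. On average, let a fraction p of active-arm patients have a booster inside a window, let no booster fall elsewhere, and let everyone attend the three core sessions. The extrapolated mean is 6p and the true mean is 3 + p. They are equal at p = 3/5 = 60%. Below that, visits are understated and the active arms are favoured.

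**4. Early ambulatory referrals (illustration; the rates are assumed)**

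Let background use be b visits per month, raised to r in the first three months. The true annual total is 3r + 9b. The extrapolated total is 6(b + b) = 12b.

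| b | r | True | Extrapolated | Share missed |
|---|---|---|---|---|
| 0.2 | 0.4 | 3.0 | 2.4 | 20% |
| 0.1 | 0.3 | 1.8 | 1.2 | 33% |
| 0.1 | 0.5 | 2.4 | 1.2 | 50% |

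These visits are under-counted rather than absent. If use does not peak early, the extrapolation is not biased by this mechanism.

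**5. Comparison with inpatient care**

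Six-month recall at months 6 and 12 covers 12 of 12 follow-up months, including all 6 counselling weeks when counselling starts at baseline.

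**The case against.** The strongest reply is that the one-month recall was written for something else. That paragraph concerns care outside the primary-level HIV and diabetes service: TB treatment, hospital, emergency and paramedic care, and mental health referral. Counselling is measured separately: counsellor time by the time and motion tool, supplies from trial data. Table 2 lists intervention utilisation apart from referral utilisation. The patient-cost section states no recall period, so session counts multiplied by a reported per-visit cost may be what the authors intend. The short recall is also a disclosed trade-off against recall bias, and utilisation rates are to be varied in sensitivity analysis.

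Much of this stands. Applying the one-month limit to the patient-cost questions is an inference, supported by the general statements in the strengths and limitations list and the Discussion. Provider-side counselling cost does not depend on patient recall. Inpatient use is fully covered and is to be validated against Department of Health data. The decision rule uses the provider-perspective ratio, in which only ambulatory referrals are touched.

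It does not remove the point. The questionnaire is the only stated source of patient resource use; the time and motion tool records counsellor time, and Table 1 covers provider costs. The Table 2 range for referral use is a 95% uncertainty interval around a mean. That describes sampling error, not a period without observation. The link between session counts and per-visit patient cost is not stated, and the recall and extrapolation rules that are stated do not supply it.

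**Conclusion.** As written, the measurement rules do not observe the core counselling sessions if counselling starts within about 15 weeks of baseline. If attendance costs are derived from the recall data, 3 core visits become 0, and a booster inside a window becomes about 6. The societal ratio then favours both active arms over treatment as usual, unless boosters fall in a window for roughly 60% of patients or more. The size in money cannot be given, because the article reports no per-visit patient cost. Early ambulatory referrals are mis-estimated to an extent that depends on how far use peaks early.

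The assumptions are prompt counselling, one-month recall for the patient-cost questions, and sixfold scaling of each follow-up window.

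A reader might infer more than this, and the documents do not support it:
- **That the whole patient cost of counselling is lost and the patient-cost objective cannot be met.** The start date and booster timing are not given, and session records with per-visit costs could supply the figure.
- **That any arm difference in ambulatory use shrinks by a third.** This would follow from averaging the pre-enrolment month equally with the two follow-up months. The article says only that the data are extrapolated, and a baseline month is an ordinary adjustment covariate.
- **That months 1 to 5 are unobserved altogether.** This is true of ambulatory use only.

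**What to change.** 1. Calculate patient attendance cost in the active arms as sessions attended (trial records) × time and travel cost per visit (questionnaire). Where a session coincides with a routine HIV or diabetes visit, apportion the shared cost by a rule fixed in advance.
2. Exclude counselling visits from the extrapolated recall data, so that they are neither double counted nor multiplied.
3. State that the month-6 window represents the first six months and the month-12 window the second six. Use the pre-enrolment month only as a baseline covariate, never as follow-up cost.
4. Acknowledge that early ambulatory referrals are unobserved. Add a sensitivity analysis that varies their rate in the first months, by arm, beyond the sampling interval in Table 2. Step 3 does not recover these visits.

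The cost is small. Session attendance is already implied by the planned dosage analysis and the intervention-utilisation parameter, and the questionnaire already asks about time and travel, so no new data collection should be needed. The drawbacks are that apportionment needs an assumption and that the societal ratio is likely to become slightly less favourable to the active arms.
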